## Abstract

**Background:**

Although patients in palliative care commonly report high emotional and spiritual needs, effective psychosocial treatments based on high quality studies are rare. First research provides evidence for benefits of psychosocial interventions in advanced cancer care. To specifically address end-of-life care requirements, life review techniques and creative-arts based therapies offer a promising potential. Therefore, the present study protocol presents a randomized controlled trial on the effectiveness of a newly developed music therapy technique that is based on a biographically meaningful song (“Song of Life”; SOL).

**Methods:**

In a design with two parallel arms, 104 patients at two palliative care units will be randomly assigned to three sessions of either SOL (experimental group) or relaxation exercises (control group). Improvements in the psychological domain of quality of life will be the primary endpoint, while secondary outcomes encompass spiritual well-being, ego-integrity, overall quality of life, and distress. Additionally, caregivers will be asked to provide feedback about the treatment. Assessment of biopsychological stress markers and qualitative analysis of perceived strengths and weaknesses will complement data collection.

**Discussion:**

Based on the results of a previous pilot study, we dedicated considerable efforts to optimizing the intervention and selecting appropriate outcomes for the present trial. We are confident to have designed a methodologically rigorous study that will contribute to the evidence-base and help to develop the potential of psychosocial interventions in palliative care.

**Trial registration:**

German Clinical Trials Register (DRKS) – DRKS00015308 (date of registration: September 07th 2018).

## Background

How to preserve the psychosocial, spiritual and existential integrity of people facing an incurable disease is considered one of the main challenges of palliative care [1]. Although palliative care aims to support terminally ill patients and their relatives on a physical, psychosocial and spiritual level [2], effective treatments have mainly been developed and investigated with a bio-medical focus on pain or dyspnea, for instance [3]. Nevertheless, psychological distress (e.g., depression, anxiety or feelings of hopelessness) and spiritual concerns (e.g., regarding purpose or meaning in life) are highly prevalent in the terminal phases of a life-threatening disease [4, 5]. Thus, the recent advances of psychosocial interventions addressing these needs offer huge potential for providing holistic palliative care [4].

Interestingly, the link between psychological and biological mechanisms in terminal disease offers an encouraging psychoneuroimmunologcial perspective for psychosocial interventions [6]. On the one hand, the stress a patient experiences can increase through the diagnosis and course of a life-threatening illness like cancer, while on the other hand stress itself can also affect disease outcomes like tumor growth, progression and metastasis [7]. The human biological stress response is primarily adaptive and consists of an increased activation of the hypothalamic-pituitary-adrenal (HPA) and the autonomous nervous system (ANS). The resulting elevated levels of circulating glucocorticoids and catecholamines can suppress immunological activities and deteriorate symptoms, especially in chronical diseases like cancer [8]. Therefore, beyond pharmacological treatments, stress-reducing psychosocial interventions have been developed and shown to improve immune function [9, 10].

Most commonly, psychosocial treatments in palliative care are categorized into cognitive-behavioral therapy (CBT), mindfulness-based interventions, life review or meaning-centered interventions, and creative-arts based therapies [11]. Although CBT has shown to improve depression and quality of life in patients with advanced cancer [12], the treatment manuals mostly fail to consider the unique conditions of end-of-life care, such as rapid physical declines or limited life expectancy [13]. Mindfulness-based interventions focus on the cultivation and practice of mindfulness (i.e., purposeful, nonjudgmental, moment-to-moment awareness) [14]. In cancer care, research has proliferated over the past decade with evidence on improvements in psychological distress and sleep disturbances as well as markers of immune function and autonomous nervous system activity [15]. Despite its potential for palliative care settings, a recent review on short-term mindfulness interventions [16] identified only a limited number of clinical trials with low quality of evidence.

To specifically address the psychological and existential distress of terminally ill patients, life review interventions such as dignity therapy [17, 18], the structured life review [19], or meaning-centered therapy [20] have recently emerged. According to developmental psychologist Erik Erikson, the central themes of the final stages of life can be outlined as generativity (i.e., producing something lasting of oneself) and ego-integrity (i.e., a retrospective sense of acceptance and meaning of one’s life) [21]. The life review techniques approach generativity and ego-integrity of terminally ill patients through creating an intellectual or physical legacy, e.g., a written transcript on the patient’s life history and hopes for their loved ones or a biographical photo book [13]. Although patients, relatives and professionals generally report high satisfaction and an improved end-of-life experience through life review interventions [17, 22], empirical findings remain inconclusive concerning reproducible effects on validated quality of life measures [23, 24]. Cumulative evidence is offered by a recent meta-analysis demonstrating moderate effects on spiritual well-being, general distress and quality of life, but with a high risk of bias [25].

Arts and music in creative-arts based therapies can also be used as a means to facilitate feelings of meaning and a psycho-spiritual integration of life experiences in terminally ill patients and caregivers [26, 27]. The use of music therapy in multidisciplinary palliative care dates back to the 1970s, when the Canadian music therapist Susan Munro as a pioneer systematically described her work with palliative patients on a physical, psychological, social, and spiritual level [28]. Nowadays, music therapy has become a widely implemented and explicitly recommended complementary therapy in palliative treatment [29]. Music therapy is generally defined as “a systematic process of intervention wherein the therapist helps the client to promote health, using music experiences and the relationships that develop through them as dynamic forces of change” [30]. In clinical palliative care practice, music therapy aims to improve quality of life through the relief of physical symptoms and psychological difficulties by offering comfort, facilitating communication and spiritual experiences [31].

Music therapy includes active techniques (the patient is actively involved in the production or reproduction of music) as well as receptive techniques (the patient listens to live or prerecorded music). Techniques in palliative care have been categorized as [32]: receptive (e.g., imagery), creative (e.g., songwriting), recreative (e.g., instrument playing) and combined (e.g., musical life review). The latter area indicates a possible synthesis of life review techniques with the help of music, especially concerning the improvement of both psychological and existential distress [32]. Despite a lack of empirical research, Sato [33] proposes a first experience-based Musical Life Review Model describing the stimuli, themes, responses, evaluation and therapeutic outcomes of this process.

While clinical practice emphasizes the benefits of music therapy in end-of-life care [28], there is still insufficient research to reliably conclude a favorable effect due to a lack of empirical investigations in both quantity and quality. Most palliative care referrals for music therapy focus on pain and quality of life with a low level of evidence [34]. For instance, music therapy has been frequently associated with pain reduction [35, 36] and enhancement of physical comfort [37, 38]. With regards to quality of life, patients receiving music therapy often report higher psychophysiological well-being [39] and subjective well-being [40] as well as improvements in emotional distress [41], anxiety and mood [36, 42, 43]. Additionally, single studies report an enhancement of spirituality [44] and lowering of salivary cortisol levels [43] after music therapy. Even family caregivers and staff members attribute music therapy an important role in the end-of-life experience [45]. However, the abovementioned studies reveal a high risk of bias (e.g. no randomization or allocation concealment, selective reporting). Thus, methodologically rigorous studies on clearly defined music therapy interventions with common outcome measures are urgently needed.

Overall, to contribute to this important but underrepresented topic of psychosocial interventions in palliative care, the general aim of the present study is to evaluate the effectiveness of the newly developed music therapy technique “Song of Life” in terminally ill patients with regard to the psychological and spiritual domain of quality of life. Based on a biographically meaningful song, SOL integrates aspects of music therapy, musical life review, and dignity therapy. In the present study, we will compare the effects of SOL to the ones of a control group which will participate in live guided relaxation exercises.

## Methods / design

### Participants and setting

This multicenter study will be conducted in parallel at two sites: The University Palliative Care Unit at the St. Vincentius Hospital in Heidelberg, Germany, and the Interdisciplinary Palliative Care Unit at the University Medical Center in Mainz, Germany. Patients admitted to these units will be screened for eligibility based on their medical record and information from personal contact. Patients are eligible for participation if they meet the following criteria: a) Palliative care according to OPS 8–982/OPS 8.98e or estimated life expectancy < 12 months, b) age ≥ 18 years, c) ability to provide informed consent, d) sufficient understanding of German language, d) clinical estimation of life expectancy > 1 week, e) no cognitive or auditory impairments (including severe psychiatric symptoms). Criteria d) and e) will be assessed by the treating physician.

Patients will be asked to name a family member, friend or other close person who is currently involved in providing assistance (subsequently called *caregiver*) whom we may contact for a caregiver evaluation of the intervention. Caregivers will be included in this study if they a) are 18 years or older, and b) show sufficient understanding of German language. All participants will be informed by the outcome assessor and need to sign consent before participation.

### Study design

The study utilizes a prospective, randomized controlled design with two parallel arms. Patients will be randomly assigned to three sessions of either music therapy (EG) or relaxation exercises (CG). We will not give information about which of the two alternative treatments is the experimental and which is the control condition. Hence, patients will be blinded with regard to the study hypotheses. It will not be possible to blind the therapists and outcome assessors, but all data will be assessed by persons different than the study therapists (i.e. study nurse, doctoral student). We will use a computer-based block randomization procedure with a block size of 8. A random sequence for group assignment will be created before the first patient is randomized. Based on this sequence, we will use the SNOSE-method [46] to conceal allocation. We expect benefits and improvements in both treatment groups with a superiority of the SOL intervention. The study design is summarized in Fig. 1.

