### Patient procedures

Eligible patients will be informed about the study goals, procedures, data protection plan, risks, and benefits. Each patient agreeing to participate and providing informed consent will undergo a baseline assessment (T0) including questionnaire data on different quality of life domains. Afterwards, a study assistant will open a serially numbered, sealed envelope containing information about group assignment. In each group, appointments will be made for three sessions of either music therapy (EG) or relaxation (CG), ideally on consecutive afternoons. Each of the three sessions is enclosed by a pre-to-post assessment of momentary distress. For both groups, the second session contains a psychobiological intra-session assessment. Post intervention data (T1) will be collected after completion of the third session including all variables assessed at baseline (T0) plus a retrospective evaluation of treatment quality. Sessions and assessments will last for approximately 45 min each day. Figure 2 depicts an overview of the timing of assessments. The interventions and outcomes will be described in detail in the following paragraphs.

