### Outcomes

Previous psychosocial research often used generic quality of life measures, palliative performance, or the concept of dignity as the primary outcome and faced difficulties in identifying significant effects on these constructs (which were operationalized including items on functional or physical state) [53]. The present SOL intervention is assumed to work on an emotional and spiritual level. Therefore, improvement in the psychological domain of quality of life (a1) is chosen as the primary patient endpoint, while the secondary outcomes encompass spiritual well-being (b1), ego-integrity (b2), general quality of life (b3), distress (b4), and the retrospective evaluation of the interventional benefits (b5). To gather additional information about the mechanisms underlying a potential effect, we will assess psychobiological markers of stress (c1) as well as subjective beliefs and attitudes towards the treatments in a qualitative interview (c2). As stated above, the family caregiver’s perspective will be captured both after the intervention and 8–16 weeks later (d1). A study assistant and a doctoral student will carry out all outcome assessment, including questionnaires, photoplethysmography, saliva samples, and caregiver interviews.

Table 1 gives an overview of the study outcomes for patients and family caregivers. The timing of assessments can be found in Fig. 2.

**Table 1 Tab1:** Study outcomes

	Primary outcome	Secondary outcomes	Exploratory analyses
Patient	• a1: Quality of life – psychological (MQOL-R, 4 items, T0-T1)	• b1: Spiritual well-being – meaning/peace (FACIT-Sp, 8 items, T0-T1) • b2: Ego-integrity (Brief Measure of Generativity and Ego-Integrity, 5 items, T0-T1) • b3: Quality of life - global (MQOL-R, 1 item, T0-T1) • b4: Distress (NCCN Distress Thermometer, 1 item, pre-post each session) • b5: Retrospective evaluation (Feedback Questionnaire, 8 Items, T1 only)	• c1: Biomarkers of stress: ▪ HPA-axis (cortisol) ▪ Sympathetic nervous system (salivary α-amylase, peripheral blood flow) ▪ Parasympathetic nervous system (HRV) • c2: Strengths and weaknesses of the intervention; Beliefs about working mechanisms (qualitative interview)
Caregiver		• d1: Retrospective evaluation (Feedback Questionnaire, 12 items, T1-T2)	

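### A single published block size of 8, with unblinded staff in overlapping recruiting, envelope-opening and assessing roles, makes up to 20% of allocations predictable and weakens concealment

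*Protocol article*

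**What the plan says.** Under Study design, the article fixes one block size: "We will use a computer-based block randomization procedure with a block size of 8". The list is made in advance ("A random sequence for group assignment will be created before the first patient is randomized") and concealed with sequentially numbered, opaque sealed envelopes: "Based on this sequence, we will use the SNOSE-method [46] to conceal allocation". The same section says of blinding: "It will not be possible to blind the therapists and outcome assessors". It adds that data are collected by people other than the study therapists.

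Three other sections assign the tasks around enrolment:

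- Participants and setting: "All participants will be informed by the outcome assessor". The treating physician judges life expectancy and cognitive or auditory impairment.
- Patient procedures: after consent and the T0 assessment, "a study assistant will open a serially numbered, sealed envelope containing information about group assignment".
- Outcomes: "A study assistant and a doctoral student will carry out all outcome assessment".

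The article states neither the allocation ratio nor whether the two sites share one list. It does not mention varying block sizes or keeping the block size from recruiting staff.

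**The concern.** An opaque envelope stops staff from reading the next assignment. It does not stop them from working it out. In a block with equal numbers per arm, once one arm has used its places, every remaining assignment in that block is known. Someone who knows the block size, has seen the earlier envelopes and talks to the next candidate can know the arm before consent is sought.

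Two things would then be at stake:

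- **Selection.** Staff could, even without intending to, bring forward or delay the approach to a patient, or explain the study differently. On a palliative ward, where a patient's condition can change quickly, this could make the arms differ in prognosis. The planned ANCOVA adjusts for the baseline score, not for unmeasured differences in prognosis.
- **Baseline measurement.** T0 precedes the opening of the envelope, which should protect it. For a predictable patient that protection is lost, and T0 is the ANCOVA covariate.

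The article's Background section itself names missing allocation concealment as a source of bias in earlier music therapy studies.

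**Working it through.** **Inputs.** Block size 8 (Study design); 104 patients at two units (Abstract, Methods). Allocation of 1:1, so 4 + 4 per block, is an assumption, because no ratio is stated. The article gives no predictability figure to reproduce. With one list, 104 / 8 = 13 complete blocks.

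**Step 1: certain allocations when staff see the whole history of their list.** There are C(8,4) = 70 possible blocks. The assignments known in advance are those in the run of identical assignments that ends the block.

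| Length of final run | Blocks (of 70) |
|---|---|
| 1 | 40 |
| 2 | 20 |
| 3 | 8 |
| 4 | 2 |

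Mean = (40×1 + 20×2 + 8×3 + 2×4) / 70 = 112 / 70 = 1.6 per block. As a share, 1.6 / 8 = 20%. Over the trial, 13 × 1.6 = 20.8 of 104 patients. The last place is always known. The last two or more are known in 30 of 70 blocks (43%).

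**Step 2: best guess under the same conditions.** The guess is always the arm with more places left, with a coin toss when they are equal. Expected correct guesses per block = 4 + (256/70 − 1)/2 = 5.33, or 5.33 / 8 = 66.6%. Over the trial this is 13 × 5.33 = 69.3 of 104, against 52 by chance.

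**Step 3: one list shared by two sites that do not exchange allocations.** Each patient is taken to arrive at either site with probability 1/2. Each site sees only its own allocations but knows where blocks start. Going through all 70 blocks and all 2^8 = 256 site patterns gives 1.25% certain (0.0125 × 104 = 1.3 patients) and a best guess right 57.5% of the time.

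**Step 4: the alternative.** This was simulated for 104 patients with sizes equally likely. The observer sees the full history, knows the set of sizes and updates by Bayes' rule.

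| Scheme | Certain in advance | Best guess correct |
|---|---|---|
| Fixed 8 (full history) | 20% | 66.6% |
| Fixed 8 (shared list, no exchange) | about 1% | about 57.5% |
| Random 4, 6, 8 (full history) | about 2% | about 68% |
| Random 6, 8, 10 (full history) | about 2% | about 66% |

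Varying the block size removes most of the certainty but hardly changes the success of guessing.

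**The case against.** The strongest reply is that concealment has been planned for. The envelopes are numbered, opaque and sealed. They are opened only after consent and T0, and a physician outside the assessment team judges part of eligibility. Even in the worst case 80% of allocations are never certain. Among common fixed sizes, 8 is also the least predictable: the certain share is 50% for blocks of 2, 33% for 4, 25% for 6 and 20% for 8. All of this stands. A reader might infer that concealment fails outright, and the article does not support that.

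A reader might also infer that one person informs patients, opens envelopes and assesses outcomes. The text shows only overlapping roles. It names an outcome assessor, a study nurse, a study assistant and a doctoral student in different places, and never says that one individual does all three tasks.

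Nor is 20% an expected value for this trial. It requires staff to know the block size and block starts and to follow every earlier allocation. Printing the size in a public article makes it available, but does not show what recruiting staff were told. The article speaks of one sequence, which could mean a list shared by both sites, where the certain share may be close to 1%.

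Finally, these figures measure predictability. They do not show that the treatment estimate would be biased, or by how much.

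A condensed article may leave list-keeping details to the full protocol. The point does not rest on such a gap. It follows from what the article does fix: one disclosed size, unblinded assessors, and an assessor who informs patients.

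**Conclusion.** The weakness is real and worth correcting, but it is one of degree. A constant, disclosed block of 8, handled by unblinded staff in overlapping roles, weakens concealment without voiding it. With 1:1 allocation, the share of allocations certain in advance lies between about 1% (one shared list, no exchange between sites, equal recruitment) and 20%, about 21 of 104 (full history, known block size and block starts). Best-guess success lies between about 57.5% and 66.6%. The article does not allow a narrower range. If staff do not know the block size or keep no tally, predictability is lower still.

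**What to change.** Generate the list with randomly varying block sizes, for example 6, 8 and 10. Do not disclose the sizes to anyone who recruits, consents, opens envelopes or assesses, and report them only after recruitment ends. State the allocation ratio and whether each site has its own list. This brings certain allocations down to about 2%, even for staff who see the full history and know the set of sizes.

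Because guessing better than chance remains possible, where existing staff allow, the person who approaches and consents patients should not have access to the allocation history. That step addresses both certainty and guessing.

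The cost is a new list and new envelopes, plus a possible small imbalance from an unfinished last block. With one list and 104 patients, an incomplete block of at most 10 leaves a difference of at most 4, that is 54 against 50. The variance factor is then 1/54 + 1/50 = 0.03852, against 2/52 = 0.03846 when balanced, an increase of about 0.15%, so the loss of power is negligible.

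The change does not address unblinded outcome assessment, which is a separate matter.

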**Fig. 1 Fig1:**
[figure not shown]
Study design. Notes: S = therapeutic session, T = time of assessment

### Patient procedures

Eligible patients will be informed about the study goals, procedures, data protection plan, risks, and benefits. Each patient agreeing to participate and providing informed consent will undergo a baseline assessment (T0) including questionnaire data on different quality of life domains. Afterwards, a study assistant will open a serially numbered, sealed envelope containing information about group assignment. In each group, appointments will be made for three sessions of either music therapy (EG) or relaxation (CG), ideally on consecutive afternoons. Each of the three sessions is enclosed by a pre-to-post assessment of momentary distress. For both groups, the second session contains a psychobiological intra-session assessment. Post intervention data (T1) will be collected after completion of the third session including all variables assessed at baseline (T0) plus a retrospective evaluation of treatment quality. Sessions and assessments will last for approximately 45 min each day. Figure 2 depicts an overview of the timing of assessments. The interventions and outcomes will be described in detail in the following paragraphs.

